**SECTION A**

**STUDY OUTLINE**

**A.1 TITLE OF PROJECT:** Utilization of portable ultrasound as a means to increase uptake of antenatal care services in rural Uganda

**A.2 SUMMARY**

Explain why this study is being conducted, using lay terminology.

*Guidance note:*

*Please convey what you think is the importance of the research and WHY it is being carried out.*

The national average for the percentage of women who go to at least on antenatal care (ANC) clinic in Uganda is close to 95%, but in the Kabale region we think it is closer to only 60%. This is thought be a result of isolated mountainous topography of villages combined with a deep mistrust of the governmental healthcare system compounded by a high reliance on traditional healers. It is well known that screening of women who are pregnant can help to detect problems that could affect the mother’s health as well as be a risk to the unborn baby. Many of these problems are treatable and some are curable, which could help the mothers and infants health. We plan to entice pregnant women on testing for HIV, syphilis, Hepatitis B, anemia (low blood count) by offering a free portable obstetric ultrasound (fOBU). If the women are found to have any of these conditions they will be provided with the appropriate management free of charge as per Ugandan Ministry of Health Guidelines.

**A.3 OBJECTIVES**

List the major objectives/hypothesis, which have governed your choice of study design

Major Objectives:

A) To improve maternal attendance at antenatal clinics and thus achieve the following outcomes by implementing routine National Ugandan screening recommendations:

i) To reduce Mother to Child Transmission of HIV

ii) Reduce Mother to child transmission of syphilis, Hepatitis B and prevent malarial complications during pregnancy

iii) Improve maternal preference for delivery with medical professionals

B) To identify antepartum risks for increased perinatal complications by offering free ultrasound. In particular, multiple birth, breech presentation, or low-lying placenta; with arrangements to be made for delivery in specialized facilities for women who are thus found to be in need.

Hypothesis of the study:

Although antenatal care in rural Uganda is hindered by geographic constraints, lack of personal finances and government health care infrastructure, cultural attitudes towards western medicine are also an important concern. Many women do not present for antenatal care as they feel that “just blood testing and tablets” are not reason enough to present for antenatal care. Offering free obstetric ultrasound will significantly increase the number of women in rural Uganda who present for antenatal care.

**A.4 METHODOLOGY**

Outline how you intend to achieve the objectives of the study.

*Guidance notes:*

*For each objective/hypothesis:-*

- *define the target population*
- *describe how the sample(s) is(are) to be recruited from the target population(s)*

*Even if the main thrust of the research is biomedical, the rationale behind your use of social science methods (e.g. patient interviews) should be clear.*

We intend to achieve the objectives of our study through two different research aspects, one focusing on non-clustered randomization (sample size of 288) and other looking specifically at randomized clusters (sample size of 550). We have clustered at the community level to observe for an effect of fOBU on increasing overall ANC attendance. We have randomized at the patient level for assessment of the efficacy of medical/dental outreach with fOBU to change patient preference for delivering in a health care center.

Communities in the Kabale District will be assessed for population size, demographics and birth rate. Communities that have similar characteristics will be selected and contacted to engage in the study. Communities who agree to participate in this study will be contacted and community leaders will make announcements at local schools, churches, and community events regarding the upcoming free antenatal clinics. During these announcements the community will be told either a) that there will be structured maternal health camps (sMHC) offering free obstetric ultrasound (OBU) or b) that there will be sMHCs with no mention of the fOBU. In actuality, to assure that all women are given the benefit of optimal care, all SMHCs will provide fOBU, but only the advertising messages will differ between groups. Communities will be stratified by catchment population (small, medium or large) prior to randomization and assignment to the intervention or control group. Additionally, we will be collecting demographic data on registration to clinic and asking a pre clinic questionnaire to assess maternal feelings towards the healthcare system, and their preferences for where to deliver their baby (at a healthcare center or at home).

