Sample size calculations were considered for two of the primary outcomes. For the first outcome – looking to determine the efficacy of portable ultrasound in improving maternal uptake of antenatal care due to portable ultrasound being offered – a simple randomization based on communities will be utilized. For the additional outcome of eliciting a change in patient preference for delivering at a healthcare facility before and after a rural outreach clinic the communities will be both clustered and randomized. In this case a design effect is added to account for the clustering for this patient-level outcome.

1. Facility based uptake of ANC (no clustering): At a two-sided alpha of 0.05 and holding power at 80%, with p1 of .70 and p2 of 0.52 [1], then 144 pregnant women will be required in each of the control and intervention groups. Inflating this by 25% to prepare for any non-consent and/or non-response, the required sample increases to 180 women per group. From experience gained in our pilot study, we anticipate that health facilities will enroll a greater number of women, therefore our sample will provide more than adequate power. We will conduct power calculations during analysis, however, we anticipate power of greater than 90%.
2. Patient-level outcomes (clustered): At a two-sided alpha of 0.05 and holding power at 80%, using an estimated intracluster coefficient (ICC) of 0.1 [2], with p1 of 0.95 and p2 of 0.85, and an average cluster size of 60 pregnant women (m), then 225 pregnant women will be required per study arm, which is equivalent to needing 4 clusters per group. Inflating this by 25% to account for potential non-response gives 282 pregnant women per group.

Notes:

1. Rate of uptake of antenatal care (at least 1 ANC visit) in pilot studies in our community
2. Generally, ICCs are not known prior to study start. For ICC assumption, it is generally accepted that clinical outcomes have ICCs of around .05; whereas process outcomes (which our research is studying) range from 0.05 to 0.15; we have used 0.1 in our calculations.

Reference: <http://www.who.int/reproductivehealth/topics/best_practices/intracluster_correlation.pdf>

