**3. Design and Methodology**

Communities in the Kabale District will be assessed for population size, demographics and birth rate. Communities that have similar characteristics will be selected and contacted to engage in the study. Communities who agree to participate in this study will be contacted and community leaders will make announcements at local schools, churches, and community events regarding the upcoming free antenatal clinics. During these announcements the community will be told either a) that there will be structured maternal health camps [sMHC] offering free obstetric ultrasound [fOBU] or b) that there will be sMHCs with no mention of the fOBU. In actuality, to assure that all women are given the benefit of optimal care, all SMHCs will provide fOBU, but only the advertising messages will differ between groups. Communities will be stratified by catchment population (small, medium or large) prior to randomization and assignment to the intervention or control group. The sMHCs will be organized in collaboration with TO – the WORLD and KIHEFO. The four-pronged approach of MTCT elimination will be followed in the design of the sMHC. This will include primary prevention of HIV, prevention of unintended pregnancies, prevention of vertical transmission and assuring linkages to care treatment and follow-up. Each sMHC will take place over a 12-hour period. All women who appear for clinic will be registered, with demographics recorded, and go through a triage process. They will then receive pre-test counseling for HIV, followed by blood sample collection for onsite testing for HIV/syphilis/hepatitis B, they will then go through family planning sessions, receive a fOBU, will be seen by a triage nurse and then be seen by an MD or DDS (Dentist) depending on their triage needs. All routine care including iron, folate and intermittent presumptive therapy for malaria will be offered free of charge. Women who are found on ultrasound screening to have potential obstetrical high risk pregnancies (low lying placenta, twins, potential birth defects) will be referred for local obstetrical services in Kabale (the regional referral center). Ultrasound will be performed using two Sonosite 180 portable ultrasonographic units operated by two technicians trained to levels of competency as dictated by national guidelines.

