**7. Statistical Design**

The study design is a cluster randomized controlled trial, whereby communities will be randomly assigned to two groups: the intervention communities will receive outreach messaging that includes information about the availability of fOBU included in medical/dental clinics and the control communities will receive outreach messaging about the availability of medical/dental clinics without mention of the availability of fOBU (although fOBU will be available in both study arms). Outcomes will be assessed at the patient-level (clustered) and the facility-level (ANC uptake).

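### The protocol contradicts itself on the unit and method of allocation: the patient-level randomisation in A.4 cannot occur, A.4 and A.5.4 reverse which outcome is clustered, and simple and stratified randomisation are both stated

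*Protocol*

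**What the plan says.** Protocol A.4 divides the study into a non-clustered part (288 women) and a randomised-cluster part (550 women). It assigns attendance to the cluster part: "We have clustered at the community level to observe for an effect of fOBU on increasing overall ANC attendance". For delivery preference it states: "We have randomized at the patient level for assessment of the efficacy of medical/dental outreach with fOBU to change patient preference".

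A.5.4 describes it differently. For uptake of antenatal care, "a simple randomization based on communities will be utilized", and the calculation is labelled as having no clustering. For delivery preference, "the communities will be both clustered and randomized", and a design effect is added.

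On how communities are allocated, A.4 and Section 3 use the same sentence: "Communities will be stratified by catchment population (small, medium or large) prior to randomization and assignment to the intervention or control group". Section 7 gives the overall design: "The study design is a cluster randomized controlled trial, whereby communities will be randomly assigned to two groups". A.7 analyses preference with a GEE model whose stated purpose is to adjust for cluster randomisation.

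A.4 and Section 3 also say that only the advertising message differs between groups and that all camps offer the ultrasound.

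**The concern.** The unit of randomisation determines what the trial can claim, how it is sized and how it is analysed. It must be settled before the first announcement and cannot be repaired in analysis. Here a reader of A.4 and a reader of A.5.4 would come away with opposite accounts of which outcome rests on clustered data. Staff carrying out the allocation could follow either a simple or a stratified scheme and be able to cite the protocol for it.

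The method matters because A.8 gives the primary objective as the number of women who present, and that number depends directly on catchment size. With about four communities per arm, an allocation that ignores size can easily place most of one size band in one arm.

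**Working it through.** **1. Can patients be randomised?** The message is given by community leaders at schools, churches and community events before the camp (A.4, Section 3, Section 8). A woman arrives already exposed to her community's message. At the camp, both arms receive the same services, including the ultrasound. No element remains that could be allocated to one woman and not to another. The A.4 statement therefore conflicts with the trial's own mechanics as well as with Section 7 and A.7.

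**2. The statements side by side.**

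| Place | Attendance / uptake | Delivery preference | Allocation of communities |
|---|---|---|---|
| A.4 | clustered by community | randomised by patient | stratified by catchment size |
| A.5.4 | no clustering | clustered, design effect added | simple |
| Section 3 | – | – | stratified by catchment size |
| Section 7 | facility-level outcome | patient-level, clustered | random, method not named |
| A.7 | health-centre regression | GEE for cluster randomisation | – |

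The totals show the same reversal. In A.5.4, 2 × 144 = 288 is the uptake sample. In A.4, 288 belongs to the non-clustered part, which by the sentences that follow is the preference part.

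**3. What stratification changes with eight communities.** Inputs: four clusters per group (A.5.4), so eight communities and C(8,4) = 70 possible 4:4 splits. Band sizes are assumptions. A draw is counted as good if no size band lies wholly in one arm.

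- Bands 3/3/2: the arm must take 1 and 2, or 2 and 1, from the two bands of three, and 1 from the band of two. Good draws: 2 × (3 × 3 × 2) = 36. The rest: 34/70 = 49%.
- Bands 2/4/2: the arm must take 1, 2 and 1. Good draws: 2 × 6 × 2 = 24. The rest: 46/70 = 66%.

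Randomising within bands, as evenly as each band allows, avoids this in both examples.

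**4. What a single community allocation does to the uptake calculation.** Inputs from A.5.4: 0.70 against 0.52, two-sided alpha 0.05, power 80%.

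- The plan's 144 per arm does not reproduce. The usual two-proportion formula gives 115 (pooled), 112 (unpooled) or 125 (continuity-corrected). Since 115 × 1.25 = 143.75, the 144 looks already inflated, and 144 × 1.25 = 180 inflates it again. That is a separate matter; none of these figures contains a design effect.
- Assume that the ICC of 0.1 and the cluster size of 60 stated for preference also hold for uptake. Design effect: 1 + (60 − 1) × 0.1 = 6.9. Requirement: 115 × 6.9 = 793.5, so 794 per arm, and 794/60 = 13.2, so about 14 communities per arm.
- Over the ICC range of 0.05 to 0.15 in A.5.4, the design effect is 3.95 to 9.85 and the requirement 455 to 1,133 per arm.
- Power at 180 per arm: 94% if clustering is ignored. With the design effect of 6.9, the effective size is 180/6.9 = 26 and power is 26% (42% to 20% over the ICC range). This is a normal approximation that makes no allowance for the small number of clusters.

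**The case against.** The best defence is that the A.4 sentence confuses the level at which an outcome is measured with the unit that is randomised. Section 7 calls the study a cluster randomised trial and A.7 fixes a cluster-adjusted analysis of preference, so no planned analysis follows from the stray sentence. This is largely fair. A reader might infer that preference will be analysed as if women had been individually randomised; A.7 does not support that. The sentence is still false as written, and the reversal between A.4 and A.5.4 remains.

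It can also be said that simple randomisation in A.5.4 is loose wording for a calculation without a design effect, since it introduces the item labelled as having no clustering. That may be so, but as written it names an allocation method that conflicts with the two methodology sections.

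Two stronger readings are tempting and should not be drawn. The first is that simple randomisation of communities gives no valid comparison. It is a valid procedure; it only leaves balance to chance. The second is that the arms are likely to be unequal in number. Tossing a coin for each of eight communities would give 4:4 in only 70/256 = 27% of draws, but the protocol does not describe coin tossing. A.5.4 plans four clusters per group, and Section 4 speaks of half the communities going without notification, so equal arms are intended.

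Finally, the plan has safeguards: communities are chosen to be similar, baseline balance is examined, and the health-centre analysis adjusts for confounders. These reduce the risk but cannot ensure balance on size with so few clusters. Details such as the number of communities per band or how the list is generated can be left to a randomisation plan.

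**Conclusion.** The protocol's account of allocation is internally inconsistent and needs correcting before communities are allocated. The contradictions on patient-level randomisation and on which outcome is clustered rest on the text alone and need no assumption. The conflict between simple and stratified randomisation is also textual. Its size, a 49% to 66% chance that some size band falls wholly in one arm, assumes eight communities, a 4:4 split and the illustrative band sizes.

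The most consequential result is indirect. Once uptake is acknowledged as an outcome of community randomisation, its stated sample size and the anticipated power above 90% have no basis. How far short they fall depends on an ICC and cluster size that the protocol gives only for preference.

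**What to change.** In A.4, delete the patient-level randomisation sentence and the reference to a non-clustered part. In A.5.4, replace simple randomisation with randomisation of communities stratified by catchment population, as A.4 and Section 3 already say. State once, and consistently in A.4, A.5.4 and Section 7, that attendance and delivery preference both arise from this single community allocation.

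The rewording itself costs nothing in the field. It does oblige the sponsor to restate the uptake sample size and power as those of a cluster randomised comparison, with an ICC and cluster size justified for uptake. Under the assumptions above this points to more communities than the four per group planned. The sponsor would then have to recruit more communities or state plainly the lower power that the planned number provides.

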**A.5 PARTICIPANTS**

Please provide the following information on the participants with/from whom you expect to be collecting data:

A.5.1 Age / Sex: (please enter the expected number in each of the boxes)

|  | Neonates  (<28 days) | Infants  (1-11 months) | Young children  (1-9 years) | Adolescents  (10-17 years) | Adults  (18 yrs & above) |
| --- | --- | --- | --- | --- | --- |
| **Males** | **0** | **0** | **0** | **0** | **0** |
| **Females** | **0** | **0** | **0** | **0** | **550** |

A.5.2 What specific measures are in place to take into account women of childbearing age?

*Guidance notes:*

*Pregnant women may have different responses to disease processes*

*The developing foetus may be particularly vulnerable in intervention trials*

The main goals and objectives of this study revolve around recruiting pregnant women. However, given that all of the interventions being offered are standard of care and not experimental or dangerous in any way there will be minimal risk to this category of patients.

A.5.3 Describe how and where the participants are to be recruited?

*Guidance notes:*

*This is distinct from the statistical sampling method described in A.4. You should outline the procedures for recruitment of each group of participants, include details on:*

- *the setting (e.g. Country, Town, District, on the ward, out-patient department ,in the home)*
- *inclusion and exclusion criteria for selection, if relevant (e.g. “Women of child-bearing age will be excluded”)*

As described above, participants will be recruited from communities in the Kabale Region by announcements that will be made by community leaders at local schools, churches, and community events regarding the upcoming free antenatal clinics.

Inclusion criteria include:

The participants to must all be residents of the Kabale Region. All pregnant women who present to one of the sMHCs will be included.

Exclusion criteria include:

Any males or non-pregnant females who attend the health camps will be excluded from the study.*

Notes:

*All participants excluded from the study will still offered free medical and dental care as part of a mobile free medical/dental clinic that will be offered in the same community at the same time but in a neighbouring location.

A.5.4 Please justify your choice of sample size (as described in A.4)

Sample size calculations were considered for two of the primary outcomes. For the first outcome – looking to determine the efficacy of portable ultrasound in improving maternal uptake of antenatal care due to portable ultrasound being offered – a simple randomization based on communities will be utilized. For the additional outcome of eliciting a change in patient preference for delivering at a healthcare facility before and after a rural outreach clinic the communities will be both clustered and randomized. In this case a design effect is added to account for the clustering for this patient-level outcome.

1. Facility based uptake of ANC (no clustering): At a two-sided alpha of 0.05 and holding power at 80%, with p1 of .70 and p2 of 0.52 [1], then 144 pregnant women will be required in each of the control and intervention groups. Inflating this by 25% to prepare for any non-consent and/or non-response, the required sample increases to 180 women per group. From experience gained in our pilot study, we anticipate that health facilities will enroll a greater number of women, therefore our sample will provide more than adequate power. We will conduct power calculations during analysis, however, we anticipate power of greater than 90%.
2. Patient-level outcomes (clustered): At a two-sided alpha of 0.05 and holding power at 80%, using an estimated intracluster coefficient (ICC) of 0.1 [2], with p1 of 0.95 and p2 of 0.85, and an average cluster size of 60 pregnant women (m), then 225 pregnant women will be required per study arm, which is equivalent to needing 4 clusters per group. Inflating this by 25% to account for potential non-response gives 282 pregnant women per group.

Notes:

1. Rate of uptake of antenatal care (at least 1 ANC visit) in pilot studies in our community
2. Generally, ICCs are not known prior to study start. For ICC assumption, it is generally accepted that clinical outcomes have ICCs of around .05; whereas process outcomes (which our research is studying) range from 0.05 to 0.15; we have used 0.1 in our calculations.

Reference: <http://www.who.int/reproductivehealth/topics/best_practices/intracluster_correlation.pdf>

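### ANC uptake is sized as if women were independent although communities are randomised, so the stated 80% and above-90% power do not hold under the protocol's own clustering assumptions

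*Protocol*

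**What the plan says.** Section A.5.4 treats two outcomes. Item 1 is headed "Facility based uptake of ANC (no clustering") and reads "At a two-sided alpha of 0.05 and holding power at 80%, with p1 of .70 and p2 of 0.52", "then 144 pregnant women will be required in each of the control and intervention groups". A 25% inflation takes this to 180 per group. The item then expects facilities to enrol more women than that, and continues: "We will conduct power calculations during analysis, however, we anticipate power of greater than 90" per cent. Item 2, on delivery preference, applies a design effect with ICC 0.1 and mean cluster size 60, and arrives at 4 clusters per group. Its note gives an ICC range of 0.05 to 0.15 for process outcomes, the kind the protocol says it studies.

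On the unit of randomisation:
- Section 7: "The study design is a cluster randomized controlled trial, whereby communities will be randomly assigned to two groups".
- A.5.4, opening paragraph: allocation for uptake is by community, and for preference the communities are clustered and randomised.
- A.4 calls the 288-woman part non-clustered, then says: "We have clustered at the community level to observe for an effect of fOBU on increasing overall ANC attendance". For delivery preference it says: "We have randomized at the patient level for assessment of the efficacy of medical/dental outreach with fOBU".
- A.7.1 compares uptake between arms at health-centre level, says analyses are adjusted for clustering, and acknowledges that clusters are few.

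**The concern.** Community leaders announce the message to whole communities, so all women in a community share one allocation. Their decisions to attend also share distance, local leadership and the quality of the announcement. A two-proportion calculation on individual women leaves out the between-community variance that the comparison of arms must overcome. Analysing uptake at facility level does not remove the problem, because the sample is then the number of communities, not 144 women.

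Item 1 also relies on larger clinic enrolment for its extra power. With the number of communities fixed, that route soon runs out.

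A.8.1 names attendance as the primary objective, and the hypothesis in A.3 is about attendance. If power is far below what is stated, a null result could be misread as showing that advertising ultrasound does not help.

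**Working it through.** **Inputs.** From A.5.4 item 1: p1 = 0.70, p2 = 0.52, difference d = 0.18, two-sided alpha 0.05, power 80%. Borrowed from item 2 and its note, because item 1 gives none: k = 4 clusters per arm, m = 60, ICC 0.05 to 0.15.

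**1. The plan's own figure, ignoring clustering.** Mean proportion 0.61.

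n = [1.960 × √(2 × 0.61 × 0.39) + 0.842 × √(0.70 × 0.30 + 0.52 × 0.48)]² / 0.18² = (1.352 + 0.571)² / 0.0324 = 114.1, so 115 per group.

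The continuity correction gives 125, the unpooled variance 112 and the arcsine method 114. None gives 144 at 80% power. Since 115 × 1.25 = 143.75, the 144 may already contain the 25% inflation, with 180 = 144 × 1.25 a second one; that is an inference. Under independence 144 per group has 88% power and 180 has 94%. The above-90% figure is therefore reached, but only with independent women.

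**2. With clustering.** Design effect DE = 1 + (m − 1) × ICC. Effective n per arm = k × m / DE. With 180 per arm in 4 communities, m = 45:

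| ICC | DE | Effective n per arm | Power, normal | Power, t on 6 df |
|---|---|---|---|---|
| 0.05 | 3.20 | 56.3 | 50-51% | 39% |
| 0.10 | 5.40 | 33.3 | 32-34% | 25% |
| 0.15 | 7.60 | 23.7 | 24-25% | 19% |

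The normal ranges span pooled and unpooled variance. The t column uses a non-central t with 2(k − 1) = 6 df and non-centrality 0.18 / √(0.4596 / effective n), where 0.4596 = 0.70 × 0.30 + 0.52 × 0.48.

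**3. Can larger clinics rescue it?** As m grows without limit, effective n tends to k / ICC:

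| ICC | 4 / ICC | Ceiling, normal | Ceiling, t on 6 df |
|---|---|---|---|
| 0.05 | 80 | 65-66% | 51% |
| 0.10 | 40 | 38-39% | 29% |
| 0.15 | 26.7 | 27-28% | 21% |

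Item 2's inflated 282 per group at 60 per cluster is 4.7, or 5 clusters. With 5 per arm at ICC 0.05 the ceiling (effective n = 5 / 0.05 = 100) is about 75-76% by the normal approximation, still below 80%.

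**4. What 80% would take with 60 women per community.** DE = 3.95, 6.90 and 9.85. Women per arm: 115 × DE = 454, 794 and 1,133, before non-response. That is 8, 14 and 19 communities per arm by the normal approximation, or 9, 14 and 20 with the t reference.

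**5. The text on units.** A.4 calls the 288 women (2 × 144) non-clustered and then says attendance is clustered by community. It claims patient-level randomisation for preference, whereas A.5.4 and Section 7 randomise communities throughout. A.5.4 gives the design effect to preference only.

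**The case against.** The strongest objection is that the size of the shortfall rests on borrowed inputs. Item 1 states neither a cluster count nor an ICC, and item 2's 4 clusters are themselves doubtful. The stated 0.95 against 0.85 needs 141 per group unclustered, and 141 × 6.9 = 973 per arm, about 17 clusters; the 225 in item 2 fits an ICC near 0.01 (141 × 1.59 = 224). This stands as a condition on the figures. But both outcomes come from the same camps, no other count is given, and the note's ICC range is stated for this type of outcome.

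Also fair: the cluster sizes used are numbers of attendees, whereas an uptake proportion needs a catchment denominator that the protocol does not give. Stratification by catchment size is ignored too, and its effect cannot be quantified here. The powers at 180 per arm are therefore illustrative. The ceiling is sturdier, because it does not depend on clinic size. A.7.1 already plans a facility-level, cluster-adjusted analysis, so the defect lies in the planned power, not in the analysis unit.

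Four stronger readings are tempting but unsupported:
- That more women per clinic could never help. At ICC 0.01, 4 × 60 per arm gives about 90% (t: 78%), and larger clinics would pass 90%. The protocol does not assume so low a value.
- That item 1 is why the sponsor thinks a few communities suffice. Item 1 names no number of communities.
- That A.5.4 is the exact reverse of A.4. It never claims patient-level randomisation for uptake.
- That the planned power calculation during analysis is power at the observed effect. The text does not say so, and a recalculation from realised clusters and ICC would be a different thing.

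**Conclusion.** The point holds as a defect in the stated power. Item 1's 80% and above-90% figures require independent women, which a community-randomised design does not provide. Conditional on 4 communities per arm and ICC 0.05 to 0.15, power at 180 women per arm runs from about half down to a quarter by the normal approximation, and lower with the t reference. Within that range larger clinics cannot reach 80% with 4 or 5 communities per arm; only more communities can.

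The 144 is a separate arithmetic error, and under independence it errs on the safe side. The contradictions within A.4, and between A.4 and A.5.4, are plain on the page and depend on no assumption.

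**What to change.** - In A.5.4, delete the no-clustering label, the 144/180 derivation and the above-90% claim; delete the matching 288 in A.4.
- State once that communities are the unit of randomisation for both outcomes. Remove A.4's description of a non-clustered part and its sentence on patient-level randomisation.
- Restate uptake power from the actual number of communities, over ICC 0.05 to 0.15, with a small-sample t reference.
- Report the confidence interval for the uptake comparison, and do not rely on any power computed at the observed effect.

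The cost is protocol wording and a much less favourable stated power. No new data are needed. The restated figure would let the sponsor decide knowingly whether to add communities.
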